### Sample Size and Power Estimates

Power calculations for the planned 1-way ANOVA were performed using G*Power Version 3.1.9.6. [34]. With 3 collapsed times of repeated measures (baseline, just-in-time, and JITAI) and assuming a within-subject correlation of 0.5, given the focus on feasibility for this study, the most effective sample size for predicting our primary outcomes (change in walking behavior and stationary time) was 17 participants with an α level of 0.05, medium-to-large effect size of Cohen f=0.32, and power of 0.8. Allowing for 15% attrition due to dropout or adherence issues, our proposed sample size is 20 participants.

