### Objective, Aims, and Research Questions

This protocol paper presents the development of the “Walking With Just-in-Time Adaptive Interventions” (WWJ) iPhone and AW app, server, and methodology for a 6-week pilot study among adults who are not meeting the 2020 WHO PA recommendations. The primary aims of the WWJ’s study are to examine the feasibility and initial impact of a 2-week JITAI approach for increasing walking behavior (ie, walking speed, distance, and duration) and decreasing stationary behavior (ie, duration of SB and idle standing) compared to a 2-week baseline observation period and a 2-week just-in-time learning period. Thus, our corresponding research questions include: (1) Is the WWJ feasible, regarding recruitment, retention, intervention fidelity, acceptability, adherence, and engagement? (2) To what extent does the just-in-time approach impact walking and stationary behavior compared to baseline? (3) How do changes in walking and stationary behaviors across a 2-week just-in-time and a 2-week JITAI approach compare to baseline?

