#### Analytic Plan

Using the latest version of JMP Statistical Software (currently JMP, version 19.01, SAS Institute Inc, 1989-2025), preliminary analyses will include baseline descriptive statistics and exploratory data analysis. Baseline characteristics of the participants (eg, self-reported MVPA minutes from the screener, demographics, behavior change constructs, anthropometrics, and resting vital signs); recruitment, enrollment, and retention rates; implementation fidelity; adherence and compliance rates; user-burden; acceptability; treatment-specific expectations of benefits and preferences will be summarized in frequency tables for categorical variables and means and SDs for quantitative variables. Qualitative responses to applicable feasibility notifications and open-ended exit surveys will be explored.

Walking behavior and stationary time measures through all 3 periods—baseline, just-in-time, and JITAI—support a 1-way within-subjects ANOVA analysis of continuous measures (eg, average bout duration, speed, distance, and stationary time per study period for each participant) to demonstrate the feasibility of effecting a change in the behavior profile throughout the WWJ study. The intended 1-way within-subjects ANOVA assumes limited outliers, normality, and sphericity, which will be assessed graphically using boxplots, the Shapiro-Wilk test, and Mauchly test, respectively. Outliers, if present, will be assessed for their potential to weaken the analysis and removed if necessary. Nonnormal data will be transformed using the Box-Cox procedure to achieve normality. If sphericity is violated, the Greenhouse-Geisser and Huynh-Feldt corrections will be used. Tukey post hoc testing will be used to explain the differences between WWJ periods. If normality cannot be approximately achieved, the nonparametric Friedman test will be used. The model will be extended to allow for covariates if data screening of other collected demographic measures (eg, education) suggests their importance.

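### The planned power of 0.8 is correct for the omnibus F test but does not carry over to the Tukey contrast that answers research question 2

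*Protocol article*

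**What the plan says.** The Sample Size and Power Estimates section names the test it sizes: "Power calculations for the planned 1-way ANOVA were performed using G*Power Version 3.1.9.6". Its inputs are three period measures per participant, a design "assuming a within-subject correlation of 0.5", and a required number that "was 17 participants with an α level of 0.05, medium-to-large effect size of Cohen f=0.32, and power of 0.8". It ties this number to the primary outcomes, which it gives as change in walking behavior and in stationary time. It then inflates for losses: "Allowing for 15% attrition due to dropout or adherence issues, our proposed sample size is 20 participants".

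The Objective, Aims, and Research Questions section sets three questions. The first is feasibility. The second is one comparison of two periods: "To what extent does the just-in-time approach impact walking and stationary behavior compared to baseline". The third sets both prompted periods against baseline: "How do changes in walking and stationary behaviors across a 2-week just-in-time and a 2-week JITAI approach compare to baseline".

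The Analytic Plan section adds the pairwise step to the ANOVA: "Tukey post hoc testing will be used to explain the differences between WWJ periods". No power is given for any pairwise contrast, and no pattern of period means is stated. The Results section reports that data collection ended with 18 participants and that the analyses are still to be completed.

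**The concern.** A significant omnibus F test says only that the three period means are not all equal. It does not say which periods differ. Question 2 needs one specific pair, and a full answer to question 3 needs two. Those answers come from Tukey comparisons, which have a stricter threshold than a single paired test and, depending on how the means are arranged, face a smaller effect than the omnibus test does.

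Because the 0.8 is attached to the primary outcomes, a reader could take a non-significant just-in-time versus baseline result as a negative finding from a study with 80% power. The results are meant to feed the design of a later randomized trial, so that reading could count unfairly against the just-in-time component.

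**Working it through.** **Inputs.** From Sample Size and Power Estimates: n = 17, m = 3 measures, correlation rho = 0.5, f = 0.32, alpha = 0.05. From Analytic Plan: Tukey for the pairs, taken here at a familywise 0.05. Added assumptions: sphericity, normal data and, for pairwise power, a pattern of means.

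**1. The plan's own figure.** For the within-subjects F test, lambda = f² × n × m / (1 − rho) = 0.1024 × 17 × 3 / 0.5 = 10.44, on 2 and 32 degrees of freedom. The noncentral F distribution gives power 0.794, which agrees with the printed 0.8. The enrolment target also reproduces: 17 / (1 − 0.15) = 20.

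**2. From f to pairwise differences.** Here f is the standard deviation of the three means divided by sigma. The standard deviation of a paired difference is sigma × √(2 × (1 − 0.5)) = sigma, so the standardized paired difference dz equals the mean difference in sigma units.

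- Equal steps (0, d/2, d): the means have standard deviation d/√6, so d = 0.32 × √6 = 0.784. Just-in-time versus baseline has dz = 0.392 and JITAI versus baseline has dz = 0.784.
- Plateau (0, d, d): the means have standard deviation d√2/3, so d = 0.32 × 3/√2 = 0.679. Both baseline contrasts have dz = 0.679.
- Just-in-time peak, then half (0, d, d/2): d = 0.784, and just-in-time versus baseline is now the extreme pair. For a given f, no pair of means can lie further apart than this.

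**3. Tukey power at n = 17.** The critical |t| is q(0.05; 3, 32)/√2 = 2.457 on 32 degrees of freedom, and the noncentrality is dz × √17.

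| Pattern (baseline, just-in-time, JITAI) | Just-in-time vs baseline | JITAI vs baseline |
|---|---|---|
| Equal steps (0, 0.5, 1) | 0.22 | 0.78 |
| Plateau (0, 1, 1) | 0.63 | 0.63 |
| Peak then half (0, 1, 0.5) | 0.78 | 0.22 |
| No just-in-time effect (0, 0, 1) | 0.02 (an error rate, not power) | 0.63 |

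Simulation with 40,000 trials per pattern agrees. It also gives the chance that both baseline contrasts are significant: about 0.21 under equal steps and 0.48 under the plateau.

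**4. Other sample sizes.** At the achieved n = 18, omnibus power is 0.82. Just-in-time versus baseline has 0.23 (equal steps), 0.67 (plateau) and 0.80 (peak then half). At n = 20 the first two are 0.26 and 0.72. Reaching 0.80 for this contrast takes 68, 24 and 18 participants under the three patterns.

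**5. The alternative to Tukey.** With exactly three periods, if any two of the pairwise null hypotheses are true, so is the third. The closed family is therefore the global null plus the three pairs, and unadjusted pairwise tests after a significant omnibus test hold familywise error. Simulated at n = 17 under sphericity, familywise error is about 0.05. Power for just-in-time versus baseline rises from 0.22 to 0.32 (equal steps) and from 0.63 to 0.70 (plateau).

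**The case against.** The strongest reply is that nothing printed is wrong. The section labels its calculation as ANOVA power, the figure reproduces, and no pairwise contrast is credited with 0.8. This stands: a reader might infer an arithmetic error, and there is none.

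A reader might also infer that power between 0.22 and 0.63 follows from the printed inputs. It does not. A value of f fixes no pattern of means, and the same inputs allow about 0.02 to 0.78 for just-in-time versus baseline. The narrower range needs a just-in-time effect between half and all of the JITAI effect. That fits the premise that adaptation improves on untailored prompts, but the protocol does not assume it. For the same reason, the complements of those powers are not rates of missing an assumed effect, because no pairwise effect is assumed. In the equal-steps case the low power mostly reflects a contrast half the size of the largest one.

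Nor do all the research questions rest on Tukey. Question 1 is descriptive, question 3 is partly served by the omnibus test, and questions 2 and 3 are worded as matters of extent and comparison, which estimates with intervals also answer. The Strengths and Limitations section puts feasibility first, concedes the small sample, and leaves adequate power to a later trial that would draw on effect sizes. That limits the harm. It does not remove it, because the sample size section still prints a power for the primary outcomes.

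Finally, Tukey is a valid and conventional method, and being somewhat conservative is not an error. The case for replacing it is a modest gain in power.

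**Conclusion.** The point holds in limited form. The 0.8 is correct for the omnibus test and says little about the contrast in question 2 or the separate baseline contrasts in question 3. With 17 participants and f = 0.32, no pattern of means brings just-in-time versus baseline to 80% under Tukey; the ceiling is 0.776. At the achieved 18, only patterns close to the most favourable one reach it (0.804 at best). The values 0.22 and 0.63 illustrate two plausible patterns and are not properties of the plan.

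All figures assume sphericity, normality, a correlation of 0.5 and complete data. This is a worthwhile and cheap improvement in what is disclosed and in the pairwise method.

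**What to change.** **Sample Size and Power Estimates.** State that 0.8 is the power of the omnibus test only. If power is printed for a pairwise contrast, name the assumed pattern of means beside it and do not present a range as following from f = 0.32.

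**Analytic Plan.** Provided outcomes have not yet been analysed, replace Tukey with the closed procedure for three periods: the omnibus test at 0.05, with the Greenhouse-Geisser correction if sphericity fails, then paired t tests at 0.05 only if the omnibus test is significant. State the matching overall and pairwise tests for the Friedman and mixed-model routes, for which the power figures here were not calculated. If outcomes have already been examined, keep Tukey, report confidence intervals and call the pairwise results exploratory.

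**Cost.** The change rewrites two paragraphs and needs no further participants or data. The unadjusted 95% intervals are not simultaneous and can disagree with the gated test, so they should be labelled as such. If correlations between periods are unequal, the paired t test can lose some power for JITAI versus baseline. Pairwise power for just-in-time versus baseline stays below 80% at n = 17 in both illustrated patterns, so the disclosure is needed whichever pairwise method is used.

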### Ethical Considerations

This study protocol aligns with the ethical standards of the American Psychological Association and was approved by the University of Delaware Institutional Review Board (IRBNet ID: 1771712-9). All eligible participants will sign an informed consent form to participate. To protect user privacy and data security, all learning models are run locally on the AW via the WWJ app. Study participants will be compensated US $50.00 via an e-gift card voucher.

## Results

Participant recruitment and enrollment began in fall 2022. Data collection was completed in 2024 with a final study sample of 18 participants. Upon completion of the analyses, the results of this study are expected to be submitted for publication. This study was initially funded in March of 2020.

## Discussion

### Principal Findings

This protocol paper outlines the development of the WWJ server and app architecture and methodology for a pilot 6-week study to promote walking behavior and reduce stationary behavior among adults who are currently not meeting the 2020 WHO MVPA recommendations [5]. The objective of this study will be to examine the feasibility and initial impact of a 2-week JITAI approach on walking and stationary behaviors compared to a 2-week baseline and 2-week just-in-time approach. The cornerstone of a JITAI is the identification of decision points, decision rules, and contextual variables, which are taken into consideration for learning and adapting to provide potential behavioral interventions [24]. Our JITAI approach will identify and integrate both contextual variables and user receptiveness learned during the just-in-time period to provide user-specific intervention notifications to walk fast, walk longer, and stand up and move around at more personalized opportune times.

To provide support for behavior change, a JITAI will distinguish opportune times by predicting whether the person requires support, the type or amount of support needed, and whether or not the support will be acted upon [24,41]. Thus, user-specific receptiveness is a key feature of a JITAI [24]. For instance, a 2023 walking-based JITAI protocol accounted for receptiveness based on users’ previous walking behavior occurring within the same 3-hour time window [42]. Our JITAI extends upon this approach by including a 2-week observation and a 2-week just-in-time “learning” period to train the learner based on user receptiveness within contexts. This unique application of the just-in-time approach—sending intervention notifications whenever a participant meets predetermined thresholds, regardless of the likelihood of receptivity—serves to prune out nonopportune or “nonactionable” moments over time. In doing so, it enables greater customization based on user- and context-specific patterns of success and nonsuccess in promoting behavior change. For example, a 2016 walking-based just-in-time study found that delivering intervention notifications when participants “overused” their smartphone, were sedentary “for a long time,” were walking, or had “just had their meals” effectively increased walking behavior. Yet, participant feedback suggested that the system should be synced with their calendars to avoid sending intervention notifications at nonopportune—and potentially embarrassing—times [43]. Notably, this study also limited its sample to participants in the TTM’s contemplation and preparation stages [43]. In contrast, our dynamic approach will allow for continued learning opportunities during the JITAI by occasionally sending intervention notifications during previously “nonactionable” times. This policy decision assumes that a user’s state of need and receptivity may change over time, potentially enabling participants to progress fluidly through applicable stages of the TTM [44].

Similarly, our JITAI approach will not impose a minimum or maximum threshold for the frequency of intervention notifications. For instance, previous JITAIs have capped their maximum daily intervention notifications to delivering only 3 [45,46] or 4 [42] instances, regardless of whether additional opportune moments will arise. Additionally, in the 2023 walking-based JITAI, intervention notifications ceased once participants achieved a predetermined step-count goal [42]. Building on this evidence, our JITAI study will leverage a flexible approach by continuing to deliver intervention notifications even after participants meet the minimum recommendation of 150 weekly minutes of MVPA. This aligns with the WHO recommendation to encourage individuals to exceed the minimum activity thresholds for additional health benefits [5].

Furthermore, our approach extends upon the current literature by passively monitoring minute-level changes in activity patterns and their environmental contexts of busy schedules, location, and weather to personalize support. This contrasts with some previously published JITAIs that rely on self-reported states or ecological momentary assessments for policy decisions on whether to send an intervention notification [27]. For instance, a 2022 JITAI protocol aimed to reduce SB by sending intervention notifications based on preferred weather conditions, which were preidentified by participants during onboarding [47]. The system also considered nearby locations deemed suitable for PA by the researchers to send intervention notifications suggesting that the participant engage in PA rather than SB at one of the reachable locations [47]. In addition, a 2022 JITAI study aimed to promote PA by sending intervention notifications based on individual states aligned with predetermined participant-indicated preferred times of day and weather forecasts [48]. Our JITAI approach extends upon these protocols by considering passively-monitored location, time of day, real-time weather conditions—including precipitation, temperature, humidity, and wind speed—as well as external scheduling logistics (eg, “busy times” due to work restrictions or doctors’ appointments). These environmental contexts have been well-documented to impact PA and SB [49,50] and were deemed important to consider by the participants in the 2016 walking-based just-in-time study [43].

Nonetheless, the collection and use of such granular personal and environmental data may raise concerns surrounding data security and privacy [51]. To mitigate these concerns, it is essential to implement robust data protection measures for JITAIs, especially those that leverage users’ personal devices. To optimize data security and privacy, our WWJ app will run its learning models locally on the AW before securely sending and storing data on our server. Additionally, all transmitted data will be encrypted end-to-end, and participants’ data will only be matched to their participant ID to foster user trust and ultimately support greater engagement and adherence to the JITAI intervention.

### Strengths and Limitations

A key strength of our JITAI approach lies in using machine learning techniques to exclusively learn behavioral patterns, environmental contexts, and receptiveness with intervention notifications sent during the just-in-time learning period. This dynamic learning process has great promise to enhance the adaptability of the intervention and potential for behavior change by evolving to meet the unique support needs and preferences of each user. To date, this study is one of only a few true JITAI approaches in which a just-in-time learning period is leveraged to systematically assess, learn from, and dynamically adapt to user receptiveness and contextualized activity patterns in real time [24,27]. A second study strength is the assessment of theoretical psychosocial variables known to be associated with PA and SB behavior change—stages and processes of PA change, PA self-regulation, and PA self-efficacy. Exploring these variables may help identify relevant behavior change constructs to inform the development of a suitable framework for refining behavioral JITAI protocols. This framework could facilitate the proactive integration of psychosocial variables with real-time adaptive learning, further enhancing JITAI personalization.

Despite these strengths, we acknowledge the potential for limitations. One possible limitation is the extent to which participants’ engagement with this study influences the potential for the server to learn. For learning to occur, the system must detect the most opportune times to deliver behavioral prompts, which is dependent upon participants meeting the preset minimum activity thresholds. In this study, we set 250 meters as the minimum threshold for detecting walking bouts with viable opportunities to walk faster or longer. As such, participants who do not meet this minimum threshold may not receive any walking intervention notifications during the just-in-time or JITAI periods, and therefore, the potential for the server to learn is likely negligible for participants who do not engage in walking bouts below this threshold. In contrast, participants regularly meeting and exceeding the minimum thresholds will likely have more successful JITAI intervention notifications due to the potential for greater system learning. Although a unique feature of this study is the just-in-time learning period, based on previous literature, the extent to which the perceived user burden of a just-in-time “learning” approach may contribute to potential participant burnout or disengagement over time is unclear. Understanding these responses to intervention notifications is essential for implementing effective behavioral JITAIs that maximize learning, user engagement, and long-term adherence without overwhelming the user. While this study’s sample size of 20 participants is relatively small, the primary focus of this study will be establishing feasibility and acceptability, rather than generating generalizable behavioral outcomes. We expect the results and corresponding effect sizes will inform an adequately powered sample size for a future randomized controlled trial.

### Anticipated Findings and Future Directions

On Wednesday, March 13, 2024, the methodology for this work was presented as a poster at the Society of Behavioral Medicine’s 45th Annual Meeting and Scientific Sessions in Philadelphia, Pennsylvania, earning the Meritorious Award for an outstanding student-authored abstract submission and research presentation. This abstract was published in the *Annals of Behavioral Medicine* [52].

It is expected that our WWJ study will demonstrate adequate feasibility and acceptability. Following this preliminary examination, we expect to expand upon this approach by considering psychosocial constructs to ground our approach in a theoretical framework and additional contextual factors, such as personal affect, personality traits, or social factors, to further impact participant engagement and receptivity for this JITAI approach for adults who are inactive. This refinement could contribute significantly to the broader field of PA interventions, offering more tailored and impactful strategies for promoting long-term behavior change across diverse populations.

### Conclusions

In conclusion, the WWJ study represents an innovative step in personalized health interventions, combining real-time contextual data with adaptive notifications to promote walking behavior and reduce stationary time among adults who are currently inactive. By demonstrating feasibility and acceptability, this work lays the foundation for future research to leverage the just-in-time “learning” period to train JITAI approaches, allowing them to dynamically adapt to user receptiveness and contextualized activity patterns in real time. This approach holds promise for developing more personalized and scalable interventions, ultimately contributing to the broader goal of supporting long-term PA and SB behavior change.

